### Analyses of mechanistic outcomes

We will conduct a similar analysis for all other continuous outcome variables (maximal and self-selected walking speed, EMG parameters, and COM-CP displacement, and ABC score). Because our outcomes are related, we will not adjust our alpha error rate, but rather, look for consistency across outcomes. We will conduct an exploratory analysis to determine whether the variability in walking balance can be explained by the initial participant characteristics (side of lesion, type of stroke, CMSA score, initial ABC score, BBS score). To conduct these analyses, we will use a step-wise least squares method of linear regression where walking balance is the dependent variable, the pre-test measurement is a covariate, and group is an independent variable.

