## Abstract

**Background:**

Following stroke, many people have difficulty activating their paretic muscles quickly and with sufficient power to regain their balance by taking quick and effective steps. Reduced dynamic balance and mobility following stroke, or ‘walking balance’, is associated with reduced self-efficacy and restrictions in daily living activities, community integration, and quality of life. Targeted training of movement speeds required to effectively regain balance has been largely overlooked in post-stroke rehabilitation. The Fast muscle Activation and Stepping Training (FAST) program incorporates fast functional movements known to produce bursts of muscle activation essential for stepping and regaining standing balance effectively. The purpose of this study is to: 1) compare the effectiveness of an outpatient FAST program to an active control outpatient physiotherapy intervention in improving walking balance following stroke, and 2) explore potential mechanisms associated with improvements in walking balance.

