The primary objective of this assessor-blinded, parallel design, randomized controlled trial is to investigate the effectiveness of an outpatient FAST program commenced within the first six months following stroke compared to an active control intervention of conventional outpatient physiotherapy (active control) that includes no targeted fast movement training for improving walking balance. As many people fall in the first few months after discharge from inpatient rehabilitation, this was thought to be an important window for this balance intervention [19]. The primary hypothesis is that improvements in walking balance (as measured with the Community Balance and Mobility Scale, CB&M [20,21]) will be larger following 12 sessions of FAST intervention compared to 12 sessions of active control intervention. The secondary hypothesis is that CB&M scores will continue to be higher in the FAST group compared to the active control group one month following the intervention. Another aim of this study is to explore potential mechanisms associated with improvements in walking balance including; improvements in walking speed, balance self-efficacy, ability to respond to internal and external perturbations to balance and associated changes in postural muscle activation. Our *mechanistic hypotheses* are that compared to the active control intervention; the FAST retraining will result in:Increased fast and self-selected natural walking speed (gait assessment);Reduced postural sway (balance perturbation assessment);Improved timing and amplitude of muscle activation (EMG onset timing, burst area and slope) during balance perturbations and gait;Increased balance self-efficacy (using Activities-specific Balance Confidence (ABC) scale).

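### The exploratory regression selects among five baseline characteristics stepwise; with about 60 participants selection is unnecessary and inflates whatever it retains

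*Protocol article*

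**What the plan says.** In the Protocol article, the section on analyses of mechanistic outcomes describes two things. The first is an ANCOVA by group for each continuous secondary outcome. The second is a regression labelled exploratory, which asks "whether the variability in walking balance can be explained by the initial participant characteristics". Five characteristics are listed: lesion side, stroke type, CMSA, baseline ABC and BBS.

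For the second the article commits to a method: "we will use a step-wise least squares method of linear regression where walking balance is the dependent variable". It adds that "the pre-test measurement is a covariate, and group is an independent variable", so the model contains treatment group and baseline CB&M as well as whichever characteristics are selected. No entry or removal threshold, shrinkage or validation is given.

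The Sample size section plans for 30 participants per group with a completed follow-up assessment, 60 in all.

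**The concern.** Stepwise selection uses the same data to choose predictors and to estimate their coefficients. A candidate is kept only when its estimate is large enough to pass the entry test, so the retained coefficients are on average too far from zero. Where candidates measure overlapping things, as CMSA, BBS and ABC plausibly do, which of them survives depends partly on chance.

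These costs are sometimes accepted when there are too many candidates for one model. That is not so here, because the article names all five in advance. At stake is a published list of baseline characteristics said to explain walking balance, with overstated effects, which readers could use to judge which patients improve.

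**Working it through.** **Inputs from the article.** n = 60; five candidates; group and baseline CB&M also in the model (taken as always retained); pre-post correlation 0.75; group effect 0.60 SD. The article gives no figure for this regression, so there is none to reproduce.

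**Assumptions.** Entry at p<0.05, with 0.15 as a looser alternative. True coefficient of one characteristic 0.20 or 0.10, in SD of follow-up CB&M per SD of the characteristic. Correlation of 0 or 0.6 among three of the candidates. Walking balance is taken to mean follow-up CB&M.

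**1. Is selection needed?** The full model has an intercept, group, baseline CB&M and five characteristics, which is 8 parameters. Residual df = 60 − 8 = 52, if each characteristic is one term. CMSA leg and foot entered separately, or stroke type in more than two categories, would cost one further df for each extra term. Nothing forces a choice among the five.

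**2. Inflation, by hand, for an uncorrelated candidate.**
- Residual SD = √(1 − 0.75²) = 0.661.
- Testing one candidate leaves 60 − 4 = 56 df, so SE ≈ 0.661/√56 = 0.0884.
- Entry at p<0.05 needs an estimate above c = 2.003 × 0.0884 = 0.177.
- Mean of the retained estimate ≈ β + SE × φ(u)/(1 − Φ(u)), with u = (c − β)/SE. The negligible lower tail is ignored.

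| Entry | True β | u | 1 − Φ(u) | Mean if retained | Ratio to truth |
|---|---|---|---|---|---|
| 0.05 | 0.20 | −0.260 | 0.602 | 0.20 + 0.0884 × 0.386/0.602 = 0.257 | 1.28 |
| 0.05 | 0.10 | 0.872 | 0.192 | 0.10 + 0.0884 × 0.273/0.192 = 0.226 | 2.26 |
| 0.15 (c = 1.460 × 0.0884 = 0.129) | 0.20 | −0.803 | 0.789 | 0.20 + 0.0884 × 0.289/0.789 = 0.232 | 1.16 |
| 0.15 | 0.10 | 0.328 | 0.371 | 0.10 + 0.0884 × 0.378/0.371 = 0.190 | 1.90 |

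**3. Inflation, by simulation, with correlated candidates.** Forward entry at n = 60, group and baseline CB&M retained, true coefficient 0.20, three candidates correlated 0.6. The retained coefficient averages 0.27 at p<0.05 entry, and the full model gives 0.20 with 95% interval coverage. A second simulation with different assumptions (correlations of 0.5 among the scales, 0.7 between BBS and CB&M, removal step included) gives 0.29 at 0.05 entry and 0.26 at 0.15. That is inflation of about 44% and 30%, and exactly the right model is found in 39% and 37% of runs.

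**4. Wrong predictor.** With a true coefficient of 0.20 and correlation 0.6, each wrong correlated candidate enters in about 9% of runs at 0.05 entry and about 17–18% at 0.15. An unrelated candidate enters at roughly the threshold itself, 5% or 15%. The excess is therefore clear at 0.05 and small at 0.15.

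**5. A figure that does not separate the methods.** With five pure-noise candidates, the chance that at least one passes 0.05 is 1 − 0.95⁵ = 22.6%. Simulation gives about 22% for stepwise entry and about 22% for at least one p<0.05 in the full model. This is ordinary multiplicity over five tests, and removing selection does not lower it.

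**The case against.** The strongest reply is that the article itself says "We will conduct an exploratory analysis to determine whether the variability in walking balance can be explained". The regression feeds no hypothesis, sample size or treatment conclusion. The primary and retention comparisons are ANCOVAs fixed elsewhere. The sizes above also rest on effects, correlations and thresholds that the article does not give. All of this stands, and it sets the weight of the point. It does not remove the point: the exploratory label lowers the claim's status but does not correct the estimates. The direction of the bias holds under every assumption tried; only its size moves.

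It can also be said that picking out the significant coefficients of a full model would inflate them just as much. That is true, and it is why the fix requires every coefficient to be reported. If block-wise entry was meant rather than data-driven selection, the wording still needs correcting. An unseen analysis plan does not settle the matter either, because the article states the method rather than leaving it open.

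Two stronger readings are tempting, and the document does not support them.
- A reader might infer that the model contains only baseline characteristics. It does not, since treatment group is in it. Restricting the candidates to baseline characteristics also suits the question this regression is set.
- A reader might infer that the mechanism aim goes unanswered, because nothing described links a mechanism measure to CB&M. The Background does state an aim to "explore potential mechanisms associated with improvements in walking balance including; improvements in walking speed, balance self-efficacy". But it then turns that aim into between-group hypotheses, which "are that compared to the active control intervention; the FAST retraining will result in" a list of changes, and the planned ANCOVAs test those hypotheses. A within-participant link to CB&M would be an additional exploratory analysis, which a fuller plan may contain. Its absence from a condensed article is not an error.

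**Conclusion.** The concern holds for the selection method and is minor. The article commits to stepwise selection among five pre-named characteristics when 60 participants can carry all five. At p<0.05 entry, retained coefficients would be overstated by about 30% for a true effect of 0.20 SD (28% to 44% across the assumptions tried) and by more than twofold for 0.10 SD. At 0.15 entry the inflation for an uncorrelated candidate is smaller, about 16% and 90%. Correlated candidates add some risk of naming the wrong one, about 9% each at 0.05 entry with correlation 0.6. The case rests on inflation and unstable choice. It does not rest on the 22% false-positive figure, nor on interval undercoverage, which was slight for retained coefficients at 0.20 SD (about 93–94%). The treatment comparisons at follow-up and retention do not depend on this regression.

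**What to change.** Replace stepwise selection with one pre-specified linear model: follow-up CB&M on group, baseline CB&M and all five characteristics entered together. State how each is coded, in particular whether CMSA leg and foot are combined and how stroke type is grouped, so that the degrees of freedom are known. Report all coefficients with confidence intervals, whatever their p-values, and label the model exploratory. Since five characteristics are examined, say that no single nominally significant coefficient will be read as established.

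The cost is a sentence or two of analysis wording. The characteristics are already collected, and neither the sample size nor the primary analysis changes. A model relating mechanism measures to CB&M could be added as an option, but this point does not require it.

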#### Dissemination plan

One of the collaborators in this study is a Knowledge Broker, hired by the Department of Physical Therapy to enhance knowledge translation. The Knowledge Broker will augment the uptake of the research findings from this current study in the clinical community. In addition to publishing the results in high quality journals and presenting findings at national and international conferences, the results will be disseminated through the funding agency, The Heart and Stroke Foundation of BC and Yukon, on their website. The authors also intend to disseminate the information through talks to local organizations including Stroke Recovery groups and will make the FAST training program freely available for download from the laboratory website.

## Discussion

The goal of this study is to determine whether an individualized physiotherapy exercise program geared to improving the speed of muscle activation (FAST) and incorporating motor learning principles is effective in retraining walking balance in an outpatient population following stroke. If effective, this novel exercise approach has the potential to significantly improve the rehabilitation strategies for walking balance, an activity which is of paramount importance for individuals following stroke. The study design and the intervention parameters have been deliberately established to optimize the generalizability the FAST program to other outpatient stroke clinical settings. Unique to this study is the focus not only on clinical effectiveness, but also mechanistic outcomes to evaluate physiological changes in walking and balance performance as well as perceived balance self-efficacy.

## Abbreviations

FAST: Fast muscle Activation and Stepping Training
CB&M: Community Balance and Mobility Scale
COM: centre of mass
COP: centre of pressure
ABC: Activities-specific Balance Confidence scale
CMSA: Chedoke-McMaster Stroke Assessment
BBS: Berg Balance Scale
EMG: electromyography
ANCOVA: analysis of covariance
